### Sample size and statistical analysis

This is a dose-finding, safety study. The sample size of 60 participants is based on the collection of sufficient safety data to estimate the risk of DLE and PK profile at each dose level, plus a cohort expansion cohort to assess recruitment feasibility within the time targets of the trial.

The escalation will proceed according to the principles of the Bayesian Escalation with Overdose Control (EWOC) approach. The maximum tolerated dose (MTD) is defined to be the dose level of melatonin that results in a probability θ=33% that a DLE will occur in the period between the initiation of IMP treatment and 100 hours after the final administration of IMP, that is, P (DLT | dose = MTD) = 33%. The expected proportion of babies treated at doses above the MTD will be controlled at a maximum of 25% (EWOC feasibility bound α, kept constant). We use the classical specification of EWOC with a two-parameter logistic curve between dose and probability of DLE .^68^ The two parameters of the re-parameterised model, γ (the MTD) and ρ (the probability of DLT at the dose level 1), are given Uniform (ie, β (1,1)) prior distributions. For γ, the range is from the lowest dose to the highest dose. For ρ the range is from 0% to θ=33%.

We will use cohorts of three patients during the dose escalation part of the study. The operating characteristics of the dose-finding design are based on DLE occurrence for three key scenarios, based on 1000 simulations of the study per scenario (see table 5) for 24 dose-finding babies in cohorts of three. The first scenario is such that the MTD is expected to be the fourth dose level (ie, γ=4) and ρ=0.1. The second scenario is one where the fourth dose level is too toxic (P (DLE | dose=4) = 51%) and the MTD is the third one. In the third scenario, the probability of DLE is generally high (ρ=0.15, P (DLE | dose=4) = 79%), and the MTD is the second dose level.

**Table 5 T5:** Operating characteristics of the Bayesian Escalation with Overdose Control (EWOC) approach

	First dose level	Second dose level	Third dose level	Fourth dose level
DLE Curve				
Scenario 1; DLE probability	0.10	0.15	0.23	0.33 (MTD)
Scenario 2; DLE probability	0.10	0.19	0.33 (MTD)	0.50
Scenario 3; DLE probability	0.15	0.33 (MTD)	0.58	0.79
Recommendation percentages (1000 repetitions). The proportions are the percentage of the simulations that recommended each dose level. For example, in scenario 1, dose level 3 was recommended in 69% of the simulated trials.				
Scenario 1; recommendation (%)	0.0	28	69	3
Scenario 2; recommendation (%)	2	50	48	0
Scenario 3; recommendation (%)	10	89	1	0

DLE, dose-limiting event; MTD, maximum tolerated dose.

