### Dose escalation procedure

The dose escalation phase (illustrated in figure 2) will assess up to four dose levels using the six potential doses listed in table 1. Participants will be allocated to a single dose level and overall, a minimum of three participants will be enrolled per dose level. AEs, based on the Neonatal Adverse Event Severity Score (NAESS)^39^ and blood samples over six time points, will be collected to measure melatonin and BACs as shown in figure 2.

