The DSMB will review the safety and PK data following the recruitment of the third baby in a cohort. The DSMB will recommend to the Trial Steering Committee (TSC) one of the following possible outcomes: (1) Recruit at the next dose level, (2) Continue recruitment at the current dose level, (3) Reduce dose to one of the previous dose levels (where relevant), or (4) Stop the trial. Dose escalation decisions will be based on both the concurrent accumulating safety (suspected DLEs) and PK data, and their predictions at the next dose level. For PK, the trial pharmacologist will develop a population-PK model to simulate the plasma melatonin levels and BACs at the next dose level. If PK modelling predicts that melatonin systemic exposure will be equal to or exceed the Cmax of 33.5 mg/L and Area under the serum concentration vs. time curve for 0-24h (AUC24) of 454.7 mg*h/L or the BAC safety threshold (<0.25 g/L), that dose level will not be opened to recruitment. For DLE predictions, a Bayesian Escalation with Overdose Control (EWOC) approach will be used. EWOC uses a statistical model to estimate the risk of DLE per dose level with the target level of DLEs set at 33% for this trial. While awaiting dose escalation decisions (from the second dose level onwards), and in the absence of DLEs in the first three babies, a maximum of three further babies can be recruited to the current dose level after approval from the DSMB. In the event of a DLE, or having recruited the three additional babies, backfilling^40^ to the previous dose level can occur while awaiting the dose escalation decision. Data acquired from additional babies will be included in a subsequent dose escalation report for review by the DSMB/TSC. Backfilling will be limited to a maximum of 15 babies in the dose escalation study.

The subsequent dose escalation will proceed to dose level 2 at a loading dose of 10 mg/kg and maintenance doses of 5 mg/kg. Subsequent doses for dose level 3 and dose level 4 will be determined by the safety and PK model prediction. Provided that dose levels 1 and 2 have not exceeded the maximum BAC safety threshold and no other dose-limiting toxicity is encountered, further escalation will be recommended. Using the parameters of a population PK model, dose escalation will be evaluated. The possible scenarios are:

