### Outcomes

The primary outcome, to identify the RP2D, is based on:

Safety: The highest dose level that has an estimated probability of DLE closest but below the target DLE level of no greater than 33%. The totality of the safety data will also be considered.PK: Achieving and maintaining putative melatonin plasma levels of at least 15–30 mg/L and ensuring BAC remains <0.25 g/L. The PKPD (dose-response curve stratified by severity of HIE) model may also be considered.

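### The EWOC prior caps the MTD at the highest dose, so no data can bring the modelled DLE risk at that dose below the 33% needed to recommend it

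*Protocol article*

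**What the plan says.** All of this is in the protocol article.

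- **Model** (Sample size and statistical analysis). The MTD is the dose level "that results in a probability θ=33% that a DLE will occur". The model is "a two-parameter logistic curve between dose and probability of DLE", re-parameterised in γ (the MTD) and ρ (the DLE risk at level 1), both with uniform priors. On the ranges: "For γ, the range is from the lowest dose to the highest dose", and "For ρ the range is from 0% to θ=33" per cent. The feasibility bound α is constant at 25%.
- **RP2D safety rule** (Outcomes). "The highest dose level that has an estimated probability of DLE closest but below the target DLE level of no greater than 33" per cent. The same item adds that all of the safety data will be considered.
- **Doses** (Dose escalation procedure). The trial "will assess up to four dose levels using the six potential doses listed in table 1". The simulations and Table 5 are laid out on levels 1 to 4.
- **Operating characteristics** (Table 5; 24 babies in cohorts of three, 1000 simulations per scenario). In scenario 1 the MTD is level 4, with a true risk of 33% there. The recommendations for levels 1 to 4 are 0, 28, 69 and 3%: "For example, in scenario 1, dose level 3 was recommended in 69% of the simulated trials". The article does not say which rule turns the posterior into the recommended level.

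**The concern.** The prior and the RP2D rule are both stated, and they conflict at the top of the dose range. If the dose carrying 33% risk cannot lie above the highest dose, the model assumes before any baby is treated that the highest dose carries at least 33% risk. An RP2D rule that asks for an estimate below 33% then excludes that dose by assumption.

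The RP2D is the primary outcome and sets the dose for the 21 to 36 babies of the expansion phase. If the top level proved well tolerated, the model would still report it as too toxic. The committees would have to override the model to use that level, and the published operating characteristics would not have warned them. If "highest dose" means Dose 6 of Table 1 instead of level 4, the same holds for Dose 6.

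**Working it through.** **1. Algebra.** Code the lowest level as 1. The model is

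logit p(x) = logit ρ + (logit θ − logit ρ)·(x − 1)/(γ − 1), with θ = 0.33, ρ between 0 and 0.33, and γ between 1 and the highest dose.

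Since ρ is below θ, the slope is positive. At the highest dose x_max, γ ≤ x_max gives (x_max − 1)/(γ − 1) ≥ 1, so p(x_max) ≥ 0.33 for every (γ, ρ) that the prior allows. Any posterior mean of p(x_max) is therefore at least 0.33. The posterior probability that x_max exceeds γ is 1, against a permitted 25%.

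**2. The plan's DLE curves.** Scenario 1 has γ = 4 and ρ = 0.10. Logit 0.10 = −2.197 and logit 0.33 = −0.708, so the step per level is 1.489/3 = 0.496. The risks are 0.100, 0.154, 0.231 and 0.330, which agree with Table 5. Scenario 2 gives 0.100, 0.190, 0.330 and 0.509. Scenario 3 gives 0.150, 0.330, 0.579 and 0.793.

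**3. The plan's recommendation percentages.** The method was a grid posterior with 8 cohorts of 3, starting at level 1, no skipping, and γ on levels 1 to 4. The recommendation rule had to be assumed: the 25% posterior quantile of γ, rounded to the nearest level.

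| Scenario | Table 5 (levels 1/2/3/4, %) | Computed (%) |
|---|---|---|
| 1 | 0 / 28 / 69 / 3 | 0.5 / 31 / 68 / 0.4 |
| 2 | 2 / 50 / 48 / 0 | 1 / 52 / 47 / 0 |
| 3 | 10 / 89 / 1 / 0 | 10 / 86 / 4 / 0 |

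The pattern agrees within about 4 points but is not exact. With γ on 1 to 6 and the same rounding, scenario 1 gives level 4 in about 45% of trials, far from 3%.

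**4. What the cap does when the data are reassuring** (γ on levels 1 to 4):

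- The smallest p(level 4) over the prior is 0.330.
- 0 DLEs in 24 babies, allocated as the model would (3, 6, 15 and 0 at levels 1 to 4): estimated level 4 risk 0.42.
- 0 DLEs in 24 babies with 3, 3, 3 and 15 at levels 1 to 4, a split that needs a committee override: 0.356.
- 0 DLEs in 300 babies at level 4: 0.332.
- True risk 5% at every level: the written RP2D rule selects level 4 in 0% of trials. Nearest-level rounding selects it in about 29%.

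**5. Table 5's 3%.** With γ capped at level 4, the written RP2D rule gives exactly 0% for level 4. The 3% must come from another rule, such as rounding up, or from another γ range.

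**6. Raising the bound.** The documents give no alternative, so an upper bound of 6 (1.5 × level 4) is an illustration. θ, α and N = 24 are unchanged.

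| Quantity (nearest-level rounding unless stated) | Bound 4 | Bound 6 |
|---|---|---|
| Level 4 selected, all levels truly 5% | about 29% | about 99% |
| Scenario 1, level 4 selected by the written rule | 0% | 37% |
| Scenario 2, babies above the MTD | 0% | about 8% |
| Scenario 3, babies above the MTD | about 4% (1.0/24) | about 17% |
| Scenario 2, selection above the MTD | 0% | about 12% |
| Scenario 3, selection above the MTD | about 4% | about 10% |
| Scenario 3, MTD selected | 86% (Table 5: 89%) | 80 to 82% |

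**The case against.** The strongest defence is that caution is deliberate in a first-in-human neonatal trial and that Table 5 discloses it. Escalation decisions also draw on PK predictions and go through the DSMB and TSC, and the RP2D takes account of all the safety data. This softens the consequence. It does not repair a numerical criterion that no data can satisfy, and Table 5 has no scenario that would let a reader see the effect.

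The 3% in scenario 1 is weak evidence of the size of the problem. It also reflects α = 25%, only 24 babies, and a true level 4 risk of exactly 33%. Read literally, the RP2D rule makes level 3 (23%) the right answer there, and Table 5 selects it in 69% of trials.

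A reader might infer more than the documents support:

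- **That a 20 mg/kg loading dose would be lost, or that phase 2 would start on a sub-therapeutic dose.** Dose level 4 is not the same thing as Dose 4 of Table 1. Only levels 1 and 2 are fixed; levels 3 and 4 are set from the safety and PK predictions, and level 3 may itself be the level aimed at the melatonin target.
- **That the RP2D always ends at least one level too low.** Table 5 selects the MTD itself in 48% and 89% of trials in scenarios 2 and 3, and rounding to the nearest level can still reach level 4.
- **That Table 5 can be reproduced in only one way.** The recommendation rule is not given, and an upper bound slightly above 4 fits about as well.
- **That escalation is barred after any DLE at levels 1 or 2, so that Table 5 simulates a different design.** The wording "no other dose-limiting toxicity is encountered, further escalation will be recommended" gives a condition that is enough for escalation, not one without which it is forbidden.

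**Conclusion.** The point stands as a conflict between two stated rules. With γ bounded above by the highest dose, the modelled DLE risk at that dose is never below 33%, so neither the RP2D criterion nor the 25% overdose bound can be met there. This is algebra and needs no simulation assumption. It holds whether the highest dose is level 4 or Dose 6; the ambiguity only decides which dose is barred.

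The size is clearest where the drug is safe: an estimated level 4 risk of about 36% after 0 DLEs in 24 babies with 15 at level 4, and selection of level 4 in 0% of trials under the written rule when every level truly carries 5%. These figures assume γ on levels 1 to 4, no skipping and a posterior-mean estimate of risk. The 29% figure also assumes nearest-level rounding. No claim about a particular mg/kg dose or about therapeutic exposure follows.

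**What to change.** - State the dose scale on which γ is defined (levels, or mg/kg covering the Table 1 doses) and what "highest dose" refers to.
- Extend γ's upper bound beyond the highest candidate dose and keep θ = 33% and α = 25%. The factor of 1.5 used above is only an illustration; the sponsor should choose the bound by simulation.
- State the rule that will select the RP2D, and re-run and restate Table 5 under that rule.
- Add a scenario in which every level is well below 33%.

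The cost is one prior bound, a new set of simulations and protocol or SAP wording; no change in sample size is needed. The statistical price, with the illustrative bound and nearest-level rounding, is more exposure and selection above the MTD in scenarios 2 and 3 and a fall in correct selection in scenario 3 to about 80 to 82%, from 89% in Table 5. Babies treated above the MTD stay under the 25% limit. The change should be made before escalation decisions rely on the model.

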### Interim review of DLEs and dose escalation decisions

Interim review of the safety and PK data will be performed as follows: (1) After each *sentinel* baby (2) After recruitment of a cohort of three infants per dose level for dose escalation decisions and (3) After a suspected DLE. The purpose of the interim review will be to affirm safety and PK. Following completion of the DLE safety window (100 hours after last IMP administration), the safety and PK data will be source-verified by the sponsor and presented to the DSMB for review. The DSMB will review the data and advise the TSC on whether dosing at the current level may continue (for example after a *sentinel* baby or DLE event) or whether a dose escalation to the next dose level is recommended (after a cohort of three babies at a dose level). For the *sentinel* baby at each dose level, no other baby may be recruited until the interim safety and PK data have been reviewed by the DSMB/TSC. For the purpose of dose escalation decisions, the trial statistician and pharmacologist will provide updated estimates of dose-limiting toxicity and PK predictions at the next dose level. In the cohort expansion phase, the safety and PK data will be reviewed after every 10 babies. No interim analysis will be performed for the secondary and exploratory outcomes.

The study will be terminated if any of the following stopping rules are satisfied:

Emergence of new therapies for HIE of greater benefit to this population.The DSMB recommends terminating the trial for safety reasons or if any evidence suggests that the risk-benefit ratio of the clinical trial is unfavourable.AEs: The incidence or severity of AEs in this study indicates a potential risk to patients taking part in the trial. Any isolated NAESS grade 5 AE (death) considered related to the IMP will result in immediate stopping of recruitment at the current dose level. No further participants will be recruited to that dose level until review by the DSMB and TSC.PK: If the observed or predicted melatonin, ethanol, or acetaldehyde levels exceed their respective Cmax cap in the *sentinel* baby, further dosing at this dose level must not proceed until DSMB/TSC review.Significant protocol deviation, lack of compliance or cooperation on the part of an investigator, which endangers the safety of the participants or the validity of the trial.

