They must have *moderate *HIE based on aEEG/EEG or Modified Sarnat Neurological Examination.In addition to plasma melatonin and BAC, acetaldehyde levels will be measured following the loading dose (at T0+2 hours) and data made available prior to subsequent maintenance dose to ensure the following PK safety limits are met:Plasma melatonin <33.5 mg/LPlasma acetaldehyde <2.2 mg/LBlood alcohol concentration <0.25 g/L.If melatonin, BACs and acetaldehyde levels are not within the stated levels or not available, no further doses will be administered. In addition, further IMP administration to the *sentinel* baby must *not *continue if the *sentinel* baby experiences a DLE.

The clinical summary, safety and PK data will be reviewed by the Data Safety and Monitoring Board (DSMB) following 100 hours after last IMP administration (‘DLE safety window’) to determine whether the recruitment to the dose level may continue. Once safety has been confirmed in the *sentinel* baby, recruitment of subsequent babies may occur in parallel. Due to logistical constraints, only melatonin levels and BACs will be measured for the remaining participants at this dose level.

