### Dose-limiting events

Suspected DLEs are defined as any events listed below considered *related* to the IMP by the attending neonatologist and site investigator:

Severe AE defined by any single event that is grade 3 and above on the NAESS^39^Serious AE (SAE)

In the event that a suspected DLE occurs, the sponsor will be notified within 24 hours and the event will be reviewed by an independent clinical reviewer. The DSMB will review the data to confirm the DLE and advise on whether to continue recruitment at the same dose level or recruit to a lower dose level. If a suspected DLE occurs in a *sentinel* baby, at the discretion of the DSMB and TSC, a second *sentinel* baby may be requested at the same dose level; however, if a further suspected DLE occurs in this second *sentinel* baby, the dose will be considered unsafe, and no further dosing will occur at this dose level or higher.

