### Participant timeline

The infusion of the loading dose of IMP will be given as soon as possible after birth (T0), once arterial and venous access has been obtained and the participant is deemed clinically stable. IMP must be administered no later than 6 hours after birth with five subsequent maintenance doses given at T0+24 hours, T0+36 hours, T0+48 hours, T0+60 hours and T0+72 hours (±1 hour) via an individual lumen of a well-placed central venous catheter or peripheral venous cannula. Screening for clinical stability, assessments and investigations will be performed in accordance with the schedule of events summarised in table 2 with a detailed schedule outlined in the supplementary materials (online supplemental table S3). Clinical stability must be confirmed within 30 mins prior to each scheduled IMP administration. Further clinical safety data during the infusion of the IMP will be collected as outlined in table 3. This includes intensive vital signs (including invasive blood pressure) monitoring every 15 mins during the loading dose, liberalising to every hour during the maintenance doses. In the event that invasive blood pressure monitoring is lost after T0+48 hours, IMP administration may continue provided the baby is not on inotropic support and has not experienced a DLE.

**Table 2 T2:** Summary schedule of events

Schedule of events	Screening and T0	T0+ 24 hours (±1 hour)	T0+ 36 hours (±1 hour)	T0+ 48 hours (±1 hour)	T0+ 60 hours (±1 hour)	T0+ 72 hours (±1 hour)	T0+day 7 (±1 day)	Hospital discharge
Informed consent	X							
Eligibility	X							
Clinical stability	X	X	X	X	X	X		
Baby demographics	X							
Maternal characteristics	X							
Pregnancy and delivery history	X							
Placental histology	X							
Physical examination	X							
Therapeutic hypothermia	X	X	X	X	X	X		
IMP administration	X	X	X	X	X	X		
Cranial ultrasound with resistance index	X	X		X		X		
aEEG/EEG	X	X	X	X	X	X		
NIRS	X	X	X	X	X	X		
Modified Sarnat neurological examination	X	X		X		X	X	X
Concomitant medications	X	X	X	X	X	X	X	X
Review of AE and SAEs	X	X	X	X	X	X	X	X
Cord/blood gas pH/base deficit	X							
Biochemistry (renal, liver profile, CRP, troponin, CK, LDH)	X	X		X		X		
Blood culture	X							
Blood gas	X	X		X		X		
Full blood count	X	X		X		X		
Clotting including fibrinogen	X							
MRI/MRS neuroimaging								
Hammersmith Neonatal Neurological Examination (HNNE)								X
Hearing screen								X
Discharge characteristics								X
General movement assessment								X

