### Study oversight and monitoring

The UCL Comprehensive Clinical Trials Unit (CCTU) is the global sponsor for the study and is responsible for the overall trial oversight across all participating countries. UCL CCTU also acts as the sponsor for sites in the UK and Ireland. In Australia, the Flinders University Clinical Trials Unit will undertake sponsor duties at the national level under delegated authority, with UCL CCTU maintaining global trial oversight.

A Trial Management Group (TMG), comprising the Chief Investigator, CCTU, Patient and Public Involvement representative and other lead investigators, will be responsible for the design, coordination and strategic management of the trial. The TSC is an independent group providing trial oversight to safeguard the interest of the trial participants. The TSC, through its independent chair, will provide overall supervision and ultimately decide on the continuation of the trial. The DSMB is responsible for safeguarding the interests of the trial participants and monitoring the data for the trial. They are the only oversight body that has access to the individual participants’ data. Through their appointed chair, the DSMB will make recommendations to the TSC on whether the trial should continue as planned. The DSMB and TSC will independently meet after each *sentinel* baby and after every cohort of three babies for dose escalation decisions. In the situation where the TSC disagrees with the DSMB’s recommendation, a meeting will be held between the TSC and the DSMB to come to a shared decision. If a consensus is not made, then advice from the MHRA will be required.

UCL CCTU will implement a structured communication process to ensure participant safety and consistent site-level actions. Formal electronic notification of all sites will occur during sponsor working hours. In the event of any safety concerns, an urgent review by the DSMB may be convened. Where necessary, recruitment may be restricted via Sealed Envelope to prevent further dose allocation, and all sites will be formally notified by the sponsor.

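### After an IMP-related death the printed rule stops only recruitment at the dose level; no rule holds the pending infusions of other babies mid-course until DSMB/TSC review.

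*Protocol article*

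**What the plan says.** All references are to the Protocol article.

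- **Interim review of DLEs and dose escalation decisions**, adverse-event item of the stopping rules: "Any isolated NAESS grade 5 AE (death) considered related to the IMP will result in immediate stopping of recruitment at the current dose level". The next sentence repeats the scope: "No further participants will be recruited to that dose level until review by the DSMB and TSC". The same section makes a suspected DLE a trigger for interim review, and has the DSMB advise the TSC whether dosing at the level may go on, naming a DLE as an example. The item after the death rule, on exposure caps in the sentinel baby, says "further dosing at this dose level must not proceed until DSMB/TSC review".
- **Dose-limiting events**: the sponsor is told of a suspected DLE within 24 hours, an independent clinician reviews it, and the DSMB is to confirm it and "advise on whether to continue recruitment at the same dose level or recruit to a lower dose level".
- **Dose escalation procedure**: once the sentinel has been cleared, "recruitment of subsequent babies may occur in parallel". Three further babies at the level and backfilling at the previous level are also possible.
- **Participant timeline**: the loading dose is followed by "five subsequent maintenance doses given at T0+24 hours, T0+36 hours, T0+48 hours, T0+60 hours and T0+72 hours".
- **Criteria for discontinuing or modifying interventions**: the listed reasons are related events, exposure caps (reached, or predicted at the next escalation), withdrawn consent and a change in the infant's own condition.
- **Study oversight and monitoring**: if there is a safety concern, "an urgent review by the DSMB may be convened"; recruitment may be restricted through the enrolment system; formal notices go to sites in sponsor working hours.

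**The concern.** The automatic consequence of a drug-related death is stated twice, each time as a stop on new babies. A baby enrolled a day or two earlier at the same dose, perhaps at another site, still has infusions scheduled. The review decides whether dosing goes on, but nothing printed says what happens to that baby's doses before the review. A site following the text as written could give the next infusion on schedule.

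What is at stake is participant safety in a first-in-human trial in critically ill newborns. The RP2D, the DLE model and the planned analyses are not affected.

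**Working it through.** **1. Does any other printed rule supply the hold?**

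- *The heading of the stopping rules* speaks of terminating the study. The death sentences give a narrower action of their own, a recruitment stop pending review, after which recruitment can resume. The heading therefore does not supply a dosing hold.
- *The DSMB's advice on whether dosing may continue* is a result of the review. It does not act before it.
- *The general adverse-event rule and the urgent review* depend on judgement; the urgent review is optional.
- *The discontinuation reasons* (an open list) and *the stability check before each dose* look at the baby concerned, or at predicted exposure at the next level. A stable baby elsewhere triggers nothing.
- *The restriction through the enrolment system* is optional and acts on recruitment and allocation.

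None requires a hold before the review.

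**2. How likely is another baby to be mid-course (expansion phase)?**

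Inputs: 21 to 36 babies in 6 months, all at the RP2D (Trial design; Cohort expansion study). Infusions start at 0, 24, 36, 48, 60 and 72 h after T0, so a baby has an infusion still to start for 72 h. Six months is 182.5 × 24 = 4,380 h. Assumption: even (Poisson) accrual, with the time of death unrelated to the other babies' arrival.

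Mean number of other babies in that window, m = N × 72 / 4,380:

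- N = 21: 1,512 / 4,380 = 0.345; 1 − exp(−0.345) = 29%.
- N = 36: 2,592 / 4,380 = 0.592; 1 − exp(−0.592) = 45%.

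Treating the number of babies as fixed gives 28% and 44%. Counting the whole 74 h course, including the last infusion while it runs, gives 30% and 46%. The result is not sensitive to these choices.

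**3. How many infusions are pending?**

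Five maintenance infusions are pending during 0–24 h, then 4, 3, 2 and 1 in successive 12 h blocks. At a random moment in the window the mean is

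(24 × 5 + 12 × (4 + 3 + 2 + 1)) / 72 = 240 / 72 = 3.33.

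**4. How many start before a review that takes R hours?**

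An infusion due at hour s starts within R hours for a fraction min(R, s)/72 of possible moments. Summing over s = 24, 36, 48, 60, 72:

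| R | Sum | Mean started | Share of 3.33 |
|---|---|---|---|
| 12 h | 5 × 12 / 72 | 0.83 | 25% |
| 24 h | 5 × 24 / 72 | 1.67 | 50% |
| 48 h | (24 + 36 + 48 + 48 + 48) / 72 | 2.83 | 85% |

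The 24 h row matters because the sponsor may be told of the event up to 24 h after it.

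**5. What would a hold cost?**

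If it lasted the rest of the course, the mean number of infusions missed per hold is m × 3.33: 0.345 × 3.33 = 1.15 to 0.592 × 3.33 = 1.97.

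No figure is given for the escalation phase. It would depend on assumed review times, backfilling and sentinel pauses that the article does not fix. The chance is zero while a sentinel is alone on treatment, and positive once babies are treated in parallel.

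**The case against.** The strongest reply is that this is a condensed article. Handling of babies already on treatment may be set out in the full protocol or a DSMB charter, and the article mentions a structured communication process with sites. The article does not say that dosing continues after a death. A related death could also readily engage the general adverse-event rule, and review after a DLE is mandatory and covers dosing. All of this is fair and lowers the weight of the point. It does not remove it: the article does not leave the consequence of a related death to another document, but states it, twice, as a recruitment stop.

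Three stronger readings are tempting and should not be adopted.

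- *That review waits 100 hours, so every pending infusion would be given first.* The section says "Following completion of the DLE safety window (100 hours after last IMP administration), the safety and PK data will be source-verified", and this follows a list that includes suspected DLEs. But suspected DLEs have their own path: 24-hour notification, independent clinical review, then the DSMB. The 100-hour timing fits the routine sentinel and cohort reviews better. What can be said is that no other timing is printed for the review after a DLE.
- *That the exposure-cap item shows the authors hold other babies' doses for a lesser event.* That item concerns the sentinel, while no other baby may be recruited at the level. In practice it holds the sentinel's own doses. It shows only that suitable wording exists.
- *That one sentence closes the gap.* A hold works only once the site knows, and reporting may take 24 hours with formal notices sent in working hours.

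An automatic hold also has a price: doses missed cannot be made up (Study intervention), and the article regards repeated doses as necessary. That argues for a short hold and a fast review rather than for leaving the interval unregulated.

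**Conclusion.** The point stands as a gap in the safety rule: the automatic action after an IMP-related death covers recruitment only, and pending infusions in other babies at that level or above are not held until the review. In expansion, given a related death, about 29% to 45% of such events would find another baby with an infusion still to start, with 3.3 of 5 maintenance infusions left on average.

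These figures rest on even accrual and are conditional on a related death. The documents give no probability for one, and the trial excludes babies judged at high risk of dying. In practice a sponsor would probably intervene, and the full protocol may say more. The change should be made, but confidence that the full trial documents lack such a hold is only moderate.

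**What to change.** In the stopping rules, replace the two death sentences with: *A death considered related to the IMP immediately suspends recruitment and all pending IMP doses at the dose level given to the baby who died and at any higher level, until expedited DSMB/TSC review.*

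Add that every site with a baby on treatment is notified at once, including outside working hours. Without this the hold cannot act during the hours that matter most.

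Naming the level given to the baby who died, and any higher level, also settles the case of a backfilled baby dying while a higher level is open or still has babies on treatment.

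The cost is a short protocol change and an out-of-hours contact route. Some babies may miss maintenance doses with no make-up, including after a death later judged unrelated: on average about 1.2 to 2.0 infusions per hold in expansion if the hold lasts the rest of the course, and fewer if the review is quick.
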